## Abstract

**Background:**

Digital media use disorder (DMUD) is a prevalent problem among young people, which can result in adverse consequences and functional impairments across multiple domains of life due to a persistent inability to regulate one’s use, which can lead to the development of psychological problems. In particular, children and adolescents who live in families that are part of the child and youth welfare system and receive support services are considered to be at high risk of developing mental disorders. It is less likely that these families will choose a therapeutic setting for the treatment of DMUD. The objective is to reduce DMUD-related symptoms and improve media use behaviour through the implementation of an app-based training programme.

**Methods:**

The efficacy of Res@t digital, initially conceived as an adjunct to child and adolescent psychiatric treatment, is to be evaluated for n= 32 children and adolescents with a media use disorder or at risk of developing this disorder, and their families enrolled in child and youth welfare services. The efficacy of the app will be evaluated in a randomised controlled trial with a waitlist control group. The primary outcome is the reduction of DMUD symptoms over a 20-week period following the onset of app training. Secondary outcomes include EEG measurements and changes in standardised psychopathological variables.

**Discussion:**

Should the Res@t app prove efficacious when compared to a waitlist control group, it would constitute an evidence-based intervention for the treatment of DMUD in children and adolescents. For high-risk families, the app could serve as a motivational tool to prompt action regarding potential DMUD and facilitates access to therapeutic facilities.

**Clinical trial registration:**

https://drks.de, identifier DRKS00033379.

## Introduction

1

### Background and rationale

1.1

As time progresses, the public healthcare system is confronted with ever new phenomena of cultural and technological progress. Such advances have been seen in the recent past in the digital media sector, where availability and attractiveness of digital media use are increasing worldwide, apparently not without harbouring health risks. So-called “Digital media use disorders” (DMUDs) refer to behavioural addictions in which the use of digital media leads to a dependency and persistent impairment of psychosocial functioning over a certain period of time (1–3). This is an umbrella term that can be used to summarise different types of media (e.g. computer, smartphone, television), usage patterns (e.g. playing video games or gaming, watching video streams, social networking) and connectivity (online on the internet or offline). Global prevalence rates (with considerable regional differences) from an international meta-analysis by Meng et al. (4) show that 17.4% of the population have a social media addiction and 6.0% a game addiction. Furthermore, 27.0% have a smartphone addiction and 14.2% have an internet addiction. As a result, the first specifically described DMUD, “Gaming Disorder” has been included in the 11th version of the International Classification of Diseases (ICD-11; icd.who.int/browse/2024-01/mms/en) with the code 6C51 and the extension predominantly online (.0) or offline (.1). 6C51 is met with all of the following criteria related to gaming behaviour: impaired control over temporal or situational aspects, neglect of other interests or activities in favour of the behaviour, persistent behaviour despite evidence of harmful consequences, manifested over a considerable period of time (continuously or in recurring episodes for e. g. 12 months), and significant impairment in areas of psychosocial functioning (e.g. family, friends or education). Other DMUDs such as social media use disorder and streaming disorder are listed under the code 6C5Y with the generic term “Other specified disorders due to addictive behaviours”. If the criteria for a DMUD are not met, but risky user behaviour is present, this can be coded with QE22 for “Hazardous Gaming” or QE2Y “Problems with other specified health-related behaviours”.

With maturing brains, adolescents are a particularly vulnerable group for DMUD due to their still developing cognitive control and responsiveness to reinforcing systems, which are widely used in digital media today (5). Especially impulsivity and depressive rumination facilitate Internet addiction in adolescents (6). The younger generation growing up with information and communication technology is also frequently exposed to digital media, which leads to multidimensional interactions, particularly with regard to the causes of and attempts to cope with psychiatric disorders (7–11). Digital media presents a number of advantages: lower barriers when it comes to difficulties in social communication and interaction, immersion allows the “escape” from stressful events into an alternative reality and compensates for the lack of reinforcement in everyday life (12, 13). In particularly severe cases, DMUD gives rise to the phenomenon of “hikikomori”, initially documented in Japan. Hikikomori individuals isolate themselves in their homes, only venturing out on rare occasions. This represents a severe form of social withdrawal in which digital media play a significant role (14).

Social factors, including poverty, social exclusion, a lack of parental competence and supervision, and inconsistent parental behaviour, have been identified as playing a role in the development of Internet Gaming Disorder (IGD) (15). In particular, in school-aged children, family factors such as family violence and poor parental care have been identified as major risk factors for IGD (16). It is often the case that children growing up in environments more susceptible to the aforementioned risk factors are referred to child and youth services for care. The provision of child and youth welfare services plays a crucial role in the well-being of children. Children placed in child welfare systems are often characterised by a high prevalence of behavioural problems that are often associated with multiple family problems, such as parental mental health issues or substance use disorders (17, 18). It is recommended that young people be provided with more accessible psychological support services that offer measures to promote healthy coping mechanisms (19). In light of the recent coronavirus pandemic, the development of appropriate programmes to prevent and reduce behavioural addictions such as DMUDs is of particular importance (20–22).

In order to meet the specific needs of adolescents with emotional disabilities and youth at special risk, the incorporation of multimedia elements and electronic performance support systems in prevention and intervention for these subgroups has proven to be more effective than traditional interventions (23, 24). In particular, for the treatment of depression and anxiety, internet-guided and unguided digital E-mental health interventions have been demonstrated to be an effective form of treatment for adolescents, with the potential to reduce symptoms and promote well-being (25–27). A blended approach, which combines online intervention with guided contact during digital training, offers multiple advantages. This is particularly relevant from the perspective of young people and their families in the context of gaming disorder (28, 29). As part of the Res@t-Consortium (www.uke.de/projekte/resat), an app was developed that is tailored to the specific needs of young people with DMUD, serving as a digital counterpart to the CBT-based Res@t offline therapy program. The goal of this study is to demonstrate feasibility and effectiveness of the intervention for adolescents at high risk with DMUD or hazardous use pattern, who are to be reached in a blended approach and motivated to participate and train with the app. Adolescents at high risk was defined as 1) family was approached by the youth welfare service because of family-related problems (e.g. long-standing conflicts, family violence, parents or youth seeking help, school absenteeism), or 2) the family had received a recommendation for contacting the youth welfare service (from school, child and adolescent psychiatry, police), or 3) the adolescent had special needs for schooling (e.g. attention problems, hyperactivity or learning difficulties). The theoretical embedding and assessment of the effectiveness of the treatment is based on Prochaska’s Transtheoretical Model of Change in Behaviour (29, 30), which is one of the most frequently used models in this field. It describes an experience of different phases of change, which begins with the stage of Precontemplation (lack of intention to change behaviour) and leads through Contemplation (intention to change behaviour in the future) to the stage of Preparation (first steps towards behaviour change), Action (performing the behavioural change) and Maintenance (maintaining the behaviour) stages. The respective individual stage is an important factor to consider when evaluating the impact of interventions.

Moreover, for a more comprehensive understanding of DMUD, its neurobiological underpinnings of these behavioural addictions should be investigated, in addition to measures of experience and behaviour. This kind of multidimensional approach is not only in line with the Research Domain Criteria (RDoC) approach, which considers psychiatric disorders through various constructs on several units of analysis (31), but also offers a chance to detect neurobiological predictors of effective treatment. In order to follow the transdiagnostic approach of the RDoC, not only DMUD diagnoses, but also hazardous use patterns that do not yet justify a DMUD diagnosis, as well as a wide range of comorbidities are included in this study. Especially in the view of DMUD as dysfunctional coping with e.g. emotional stress, “pure” DMUD diagnoses (no comorbidities or precursors of the diagnosis) would exclude parts of the target group in need of support and distort the therapeutic effect of the intervention in real practice. For this reason, no comorbidities are excluded, with the exception of those that make participation in the study impossible. The domains investigated are addiction-related, such as positive valence (reward responsiveness, learning, and valuation) and cognition (cognitive control). In order to take the neurobiological basis into account and investigate fundamental mechanisms, the analysis levels circuits and physiology are examined by means of electroencephalography (EEG) in addition to self-reports, behaviours and paradigms.

### Objectives and trial design

1.2

In accordance with the Res@t consortium’s plan, the efficacy and effectiveness of the digital health intervention “Resource-Strengthening Training for Adolescents with Problematic Digital-Media Use and their Parents” (Res@t digital) will be examined. The aim of this training is to reduce the mental health problems associated with DMUD in adolescents and to strengthen parental self-efficacy. In order to shed light on various aspects of such a novel care programme, high-risk groups within child and youth welfare services are being investigated in this additional study alongside a main study (31). As an addition, this study supplements the main study by recording potential neurophysiological changes using EEG.

Participants will be randomised-controlled with a 1:1 allocation ratio into two arms of parallel groups, consisting of an intervention group (IG) and a waitlist control group (CG). Both groups receive the treatment as usual (TAU), meaning the standard child and youth welfare programme, while the IG additionally receives the Res@t digital intervention during the study period. Each subject in the CG will be given the opportunity to receive the training after full participation following the last data collection.

Our trial aims to test the hypothesis of the superiority of Res@t digital combined with child and youth welfare service through a greater reduction in the symptoms of the most prominent DMUD or hazardous use pattern in the individual adolescent, compared to child and youth welfare service alone. Primary hypothesis: Res@t+TAU reduces symptoms of specific DMUD in adolescents compared with TAU alone, measured as a group-by-time interaction over 5 measurement points from screening to a 10-week follow-up. Secondary hypotheses: a) Res@t+TAU reduces symptoms of specific DMUD in adolescents as assessed by their parents compared with TAU alone, measured as a group-by-time interaction over 5 measurement points from screening to a 10-week follow-up. b) Res@t+TAU reduces symptoms of specific DMUD in adolescents assessed by authorised personnel compared with TAU alone, measured as change from screening to post-intervention. c) Res@t+TAU will have a beneficial influence on several observation-based constructs related to DMUD in adolescents (improved readiness to change and sleep quality), in parents (improved life satisfaction and family self-efficacy) and in both adolescents and parents (reduced stress levels and improved family functioning and mindfulness) compared with TAU alone, measured as change from baseline to post-intervention. d) Res@t+TAU reduces DMUD typical or potential markers in the EEG compared with TAU alone, measured as change from baseline to post-intervention.

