#### Primary outcome

2.5.1

The primary outcome is the difference in the severity of specific DMUD or hazardous use pattern between IG and CG within 20 weeks of enrolment, measured at 5 time points (screening, interim, post-intervention, follow-up 1 and 2) at 5-week intervals. It is assumed that the group using the app (IG) shows bigger decreases in DMUD or hazardous use pattern compared to the group without (CG). In the event that an individual shows more than one DMUD or hazardous use pattern, the severity is operationalised by the supervising study team with the most severe type of DMUD or hazardous use pattern (gaming, social media or streaming). In order to assess gaming, social media and streaming as key areas of digital media consumption, the GADIS-A/-P, SOMEDIS-A/-P and STREDIS-A/-P are used to identify disordered or hazardous media use (33–38). All three questionnaires are based on the ICD-11 criteria for gaming disorder and other specified disorders due to addictive behaviours, which are specified here as social media use disorder and streaming disorder. The questionnaires consist of 4 items cognitive-behavioural symptoms (CBS) of problematic media use, 5 items negative consequences (NC) and one item on the frequency of these difficulties, with the exception of STREDIS-A/-P, in which CBS and NC account for 3 and 6 items respectively. If the cut-offs for CBS and NC are reached and the time criterion is met, disordered media use is indicated. If only the cut-off for CBS is reached, but not for NC, hazardous media use is assumed. If only NC but no CBS is present, another mental disorder may be present. In addition, a clinical interview to diagnose the presence of disordered or hazardous media use according to ICD-11 is assessed (at Screening and Post-Intervention) by authorised personnel. In order to take the high-risk sample into account, the assessment times were set more closely compared to the main study (32) and the baseline, post-intervention and follow-up assessments were supplemented by a measurement with GADIS-A/P, SOMEDIS-A/P and STREDIS-A/P interim (5 weeks after baseline in the middle of training) and an additional follow-up (5 weeks after the end of training and 5 weeks before the original follow-up). The interval of the DMUD questionnaires is therefore shortened from every 10 weeks to every 5 weeks (see participant timeline).

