### Data collection, management, and analysis

2.9

The data is collected continuously using the Res@t app with the ISO-certified Embloom platform as the backend. Furthermore, the PsychoEQ programme, which facilitates the collection of questionnaire data via mobile phones, tablets and personal computers, is employed. All data pertaining to participants will be pseudonymized.

Descriptive statistics are presented separately for each group and for the total sample. The data will be analysed using IBM SPSS 28 Statistics. A complete-case analysis will be conducted on the main outcome variable, the specific DMUD score, which will be evaluated at five points in time: baseline, interim, post-intervention, follow-up 1, and follow-up 2 (see **Table 1** and **Figure 2**). In order to determine whether there are notable differences in the impact of the treatment, a mixed ANOVA will be used, with the specific DMUD scores serving as the dependent variable and time and group serving as the within-subject factors and between-subject factors, respectively.

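### The only confirmatory test is a non-directional 4-df group-by-time interaction, so a significant result does not by itself establish the directed superiority that the protocol sets out to show

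*Protocol article*

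**What the plan says.** Objectives and trial design (1.2) sets out to "test the hypothesis of the superiority of Res@t digital combined with child and youth welfare service through a greater reduction in the symptoms". Primary outcome (2.5.1) repeats the direction: the app group "shows bigger decreases in DMUD or hazardous use pattern compared to the group without (CG"). The same section places the comparison "within 20 weeks of enrolment, measured at 5 time points (screening, interim, post-intervention, follow-up 1 and 2) at 5-week intervals", without singling out any visit.

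The test is fixed consistently in three places:

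- Section 1.2 has the primary hypothesis "measured as a group-by-time interaction over 5 measurement points from screening to a 10-week follow-up".
- Sample size (2.6) is computed for the within-between interaction of a repeated-measures ANOVA, with effect size 0.20, alpha 0.05 and power 0.8. This gives 32 participants, 16 per group, and 64 to be recruited.
- Data collection, management, and analysis (2.9) says that "a mixed ANOVA will be used, with the specific DMUD scores serving as the dependent variable", with time as the within-subject factor and group as the between-subject factor. The threshold is p < 0.05, and all other outcomes are exploratory.

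Section 2.9 also plans a baseline-adjusted linear mixed model, but only as a sensitivity analysis if values are missing. No section names a contrast, visit, slope or adjusted mean difference that decides the primary question.

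**The concern.** The claim has a sign and the test does not. The interaction F test asks whether the two mean profiles over five visits are parallel. Any departure from parallel counts against the null: a benefit, a harm, a temporary gap, or curves that cross. The F statistic has no sign and no single effect estimate with an interval.

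This is the only confirmatory test in the trial, and the Abstract says that an efficacious result would make the app an evidence-based treatment. If the test is significant, someone must then decide which visit or comparison shows the benefit. The trial is unblinded (2.8), and that choice would be made after the data are seen.

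**Working it through.** **Inputs from the protocol.** Two groups, five visits (1.2, 2.5.1); N = 32, 16 per group, effect size 0.20, alpha 0.05, power 0.8 (2.6).

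**Assumptions, not in the protocol.** The effect size is Cohen's f; the correlation between visits is rho = 0.5 (compound symmetry); sphericity holds (epsilon = 1).

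**1. Reproducing the planned N.** Numerator df = (2 − 1)(5 − 1) = 4. Denominator df = (32 − 2)(5 − 1) = 120. Noncentrality λ = f²·N·m/(1 − rho) = 0.04 × 32 × 5/0.5 = 12.8. Power is 0.814; at N = 30 it is 0.783. So N = 32 reproduces, and 32/(1 − 0.5) = 64. The trial was sized on the 4-df test.

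**2. What the test responds to.** Let d be the group difference at each visit in SD units, positive when it favours the intervention. With n = 16 per group, λ = (n/2)·Σ(d − mean d)²/(1 − rho) = 16·Σ(d − mean d)². Only squared deviations enter, so reversing every sign changes nothing.

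| True pattern (first visit, weeks 5, 10, 15, 20) | Σ(d − mean d)² | λ | P(reject) |
|---|---|---|---|
| Sustained benefit: 0, 1, 1, 1, 1 | 0.80 | 12.8 | 0.81 |
| Mirror-image harm: 0, −1, −1, −1, −1 | 0.80 | 12.8 | 0.81 |
| Crossing: 0, −0.45, −0.45, +0.45, +0.45 | 0.81 | 12.96 | 0.82 |
| Transient: 0, 0.5, 1, 0.5, 0 | 0.70 | 11.2 | 0.75 |

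In the crossing pattern the differences after the first visit average exactly zero. Simulation (4,000 trials per scenario) gave 0.819 for sustained benefit, 0.816 for the mirror-image harm, and 0.047 under the null.

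**3. A signed alternative.** Take the baseline-adjusted difference averaged over the four later visits. The variance of the four-visit mean is 0.25 + 0.75 × 0.5 = 0.625. Adjusting for the first visit removes rho² = 0.25, leaving 0.375. The standard error is √((2/16) × 0.375) = 0.2165, with 29 df. Patterns scaled to the planned f = 0.20:

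| Pattern | Interaction, 4 df | Adjusted average, 1 df |
|---|---|---|
| Immediate and sustained, 1 SD | 0.81 | 0.99 |
| Ramp to 1 SD by week 10, then held | 0.81 | 0.97 |
| Linear to 1.13 SD at week 20 | 0.81 | 0.88 |

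For the transient pattern in step 2 the average difference is 0.5, the noncentrality is 0.5/0.2165 = 2.31 and power is 0.61, against 0.75 for the interaction.

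**4. Where the gain comes from.** For a sustained 0.5 SD effect at N = 32, λ = 16 × 0.20 = 3.2 and the interaction has power 0.25. The unadjusted 1-df contrast (mean of the later visits minus the first) has standard error √((2/16) × 0.5 × 1.25) = 0.2795 and power 0.41. The baseline-adjusted contrast has 0.61. Of the gain of 0.36, 0.16 comes from using one degree of freedom and 0.20 from baseline adjustment.

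**The case against.** Several points stand against a harsher reading.

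- **A reader might infer that the planned test wastes power.** The documents do not support that as a general statement. The trial meets its nominal power for the test it declares. A 1-df contrast does better only if it fits the true pattern: under a linear effect the unadjusted mean-change contrast has 0.69 against 0.81 for the interaction, and under a sustained effect an unadjusted week-20 change score has 0.78. More than half of the gain in step 4 comes from baseline adjustment. The 0.5 SD used there is also half of the sustained effect that f = 0.20 implies at rho = 0.5.
- **A reader might infer that significance without a week-20 difference is a failure of the test.** The protocol does not make week 20 its primary time point; it speaks of the whole 20-week window. A benefit that fades is still a difference within that window. The averaged contrast also rejects in about 61% of trials in the transient example.
- **The direction will be visible.** Group means by visit will be reported, and a two-sided 1-df test also has its sign read off. This is fair, but a 1-df test has one sign and one interval. The interaction can combine visit differences that point opposite ways, and no rule says which one counts.
- **Follow-up contrasts are often left to an analysis plan.** That is true of detail. Here the hypothesis, sample size and analysis sections all fix a test that does not match the claim, so the issue is more than an omission.

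**Conclusion.** The concern holds as a mismatch between a directed hypothesis and a non-directional confirmatory test. A significant interaction would show that the two courses differ somewhere. It would not show that Res@t reduces symptoms, nor when. At N = 32 the test rejects with probability of about 0.81 for a 1 SD sustained benefit and for the same-sized harm, and about 0.82 for a crossing with zero average difference.

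The equality of benefit and harm follows from the form of the F test and needs no assumption about correlation. The probabilities do depend on rho = 0.5, compound symmetry and epsilon = 1, none of which the protocol states. The N for 80% interaction power would be 44 at rho = 0.3, 20 at rho = 0.7, and 38 at epsilon = 0.75 with rho = 0.5. The conclusion concerns what the result can mean; it does not say that the planned sample size is wrong for the planned test.

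**What to change.** In sections 1.2, 2.6 and 2.9, name one signed 1-df contrast as primary, with its 95% confidence interval, from the baseline-adjusted mixed model already described in 2.9. One option is the intervention-minus-control difference in the specific DMUD score, averaged over weeks 5, 10, 15 and 20, which matches the stated window. A single named visit would also serve; the protocol does not decide between them, so the sponsor should choose before unblinded data are examined. Claim superiority only if the interval excludes zero in favour of the intervention. Report the omnibus interaction and the visit-wise differences as supportive.

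One point of wording: if the first visit enters that model only as a covariate, a constant benefit over the later visits appears in the averaged group difference and not in the interaction term. The text should therefore name the contrast itself.

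The cost is a change of wording and a restated sample-size justification, with the target difference in SD units and the assumed correlation written down. No extra participants, visits or measurements are needed. The averaged contrast gives up power for a purely transient effect (about 0.61 against 0.75) and gains it for sustained ones (0.88 to 0.99 against 0.81 at the planned effect size).

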On the other hand, we expect a greater increase in the IG for family functioning, family communication and mindfulness in adolescents and parents as well as an increase in family self-efficacy and quality of life of the parents. Family functioning is assessed using the five items giving the questionnaire its name: Adaptability, Partnership, Growth, Affection and Resolve, referred to as Family APGAR (45, 46). The family communication scale (FCS) measures “the act of sharing ideas, participating in decision making, and expressing feelings among members as a family unit” through ten items by self-assessment (47–49). Family functioning and communication are self-assessed by adolescents and parents. Family self-efficacy in parenting is measured by parents in the questionnaire with the same name (Familiäre Selbstwirksamkeit [FSW]) using nine items (50). The Mindful Attention Awareness Scale (MAAS-5) measures mindfulness (a state of mind characterised by receptivity, in which the subject is able to observe their thoughts, feelings and surroundings non-judgementally, thereby being present in the moment) in five items in adolescents and parents (51, 52). The Ulm Quality of Life Inventory for Parents (ULQIE) is used to assess parents’ life satisfaction over the last seven days (53). The 29 items of the ULQIE are partially incorporated into the subscales of physical and daily functioning, satisfaction with family support, emotional strain due to the child’s illness, self-development and well-being. All of the above mentioned questionnaires are collected at baseline and post-intervention.

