To measure neurophysiological characteristics of brain activity, an EEG is used. For this purpose, a resting-state EEG (rsEEG) with 5 minutes of eyes open and 5 minutes of eyes closed is recorded at the beginning, followed by approx. 6 minutes of an oddball paradigm. A 30-minute sequence of a favoured media related activity (e.g. gaming) follows. The EEG is therefore carried out in the participants’ homes using a mobile EEG. The EEG ends with another rsEEG identical to the one at the beginning of the recording (see **Figure 1**). 45 minutes are planned for the preparation of a 32-channel montage. The oddball task is active visual and administered as described in Kappenman et al. (60). Participants are presented with the letters A, B, C, D and E in random order in a trial. In each block, one of these letters is defined as a target, which must be distinguished from the nontargets by pressing the up and down arrow keys using the dominant hand. There are a total of 5 blocks, each with 40 trials, in which each letter is presented 8 times. Each stimulus is presented for 200 ms and the inter-stimulus interval is 1,200 to 1,400 ms. The first EEG is carried out in the period from screening to the start of training and a further EEG after the end of training.

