**Figure 2 f2:**
[figure not shown]
Study flowchart of participants. DMUD, digital media use disorder; EEG, Electroencephalography; TAU, treatment as usual.

**Table 1 T1:** Measurement time points.

[figure not shown]

Time points: t_0_ = Screening (< week 0), t_1_ = Baseline (week 0), t_2_ = Interim (week 5), t_3_ = Post-intervention (week 10), t_4_ = Follow-up 1 (week 15), t_5_ = Follow-up 2 (week 20). GADIS-A, Gaming Disorder Scale for Adolescents; SOMEDIS-A, Social Media Disorder Scale for Adolescents; STREDIS-A, Streaming Disorder Scale for Adolescents; SDQ, Strength and Difficulties Questionnaire; PSQI, Pittsburgh Sleep Quality Index; ISI, Insomnia Severity Index; ESS-CHAD, Epworth Sleepiness Scale - Children and Adolescents; PSS-10, Perceived Stress Scale; Family APRGAR, Family Functionality; FCS, Family Communcation Scale; MAAS-5, Mindfulness Attention Awareness Scale; FEVER, Questionnaire for the Assessment of Readiness to Change; EEG, Electroencephalography; GADIS-P, Gaming Disorder Scale for Parents; SOMEDIS-P, Social Media Disorder Scale for Parents; STREDIS-P, Streaming Disorder Scale for Parents; SDQ-f, Strength and Difficulties Questionnaire – External Assessment; PHQ-9, Patient Health Questionnaire; GAD-7, Generalized Anxiety Disorder Questionnaire; EEI-R, Parenting Inventory - Revised; FSW, Parental Self-Efficacy; ULQIE, Ulm Quality of Life Inventory for Parents of Chronically Ill Children.

In the event of missing values, a sensitivity analysis will be conducted in accordance with intention-to-treat principles. Missing values will be assumed to be missing at random and handled using the multiple imputation method. A baseline-adjusted linear mixed model will be calculated with random intercept for patient, group and timepoint as well as their interaction as main effects and respective baseline value as covariate. The threshold for statistical significance of the primary outcome is set at p < 0.05. Further outcomes are analysed in an exploratory manner.

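### Read as written, the exploratory questionnaire and EEG comparisons (hypotheses c and d) use change scores without a baseline covariate; adding the baseline already collected would gain precision at no cost.

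*Protocol article*

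**What the plan says.** Section 1.2 (Objectives and trial design) gives the measure for hypothesis c (readiness to change, sleep, stress, family and parental scales, mindfulness) and for hypothesis d (EEG markers) in the same terms: "measured as change from baseline to post-intervention". No covariate is mentioned.

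The starting values are there to be used. For the family, mindfulness and parental quality-of-life scales, section 2.5.2 says "All of the above mentioned questionnaires are collected at baseline and post-intervention". For EEG it says "The first EEG is carried out in the period from screening to the start of training and a further EEG after the end of training".

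Section 2.9 names two models:
- **Main analysis, for the DMUD score:** "a mixed ANOVA will be used, with the specific DMUD scores serving as the dependent variable", with time as within-subject factor and group as between-subject factor. There is no baseline covariate.
- **Sensitivity analysis in the event of missing values:** "A baseline-adjusted linear mixed model will be calculated with random intercept for patient, group and timepoint", their interaction, and the "respective baseline value as covariate".

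For everything else, section 2.9 says only "Further outcomes are analysed in an exploratory manner".

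**The concern.** A difference in raw change carries the full noise of the baseline measurement. It also takes in any chance difference between the arms at baseline: the arm that starts higher tends to fall more through regression to the mean, whatever the treatment does. Both effects are strongest when the baseline-to-post correlation is low and the groups are small.

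Both conditions are plausible here. The plan expects 32 evaluable participants, 16 per arm. The Discussion concedes that recording EEG at home may lower its reliability, which would tend to lower the correlation. EEG is also what this study adds to the main Res@t study. What is at stake is the precision of all comparisons under c and d, although the plan already contains a model that would recover it.

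**Working it through.** **The plan's own figure.** Section 2.6 gives effect size f = 0.20, alpha 0.05, power 0.80, two groups and five measurements. The correlation among repeated measures and the sphericity correction are not stated; 0.5 and 1 are assumed.
- Noncentrality: f² × N × m / (1 − rho) = 0.04 × 32 × 5 / 0.5 = 12.8.
- Degrees of freedom: (2 − 1)(5 − 1) = 4 and (32 − 2)(5 − 1) = 120.
- Power is 0.814 at N = 32 and 0.783 at N = 30, so 32 is reproduced. Recruitment is 32 / (1 − 0.5) = 64, also as stated.

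This calculation covers the primary outcome only. None is given for c or d.

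**What the stated main model would do at two time points.** With only a baseline and a post value, the group-by-time test of a mixed ANOVA is the two-sample test on change scores, without adjustment. Extending the section 2.9 main model to c and d would therefore give an unadjusted change comparison.

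**Variance of the two comparisons.** Assume equal SD s at both times and baseline-to-post correlation rho. Per-person variances are:
- unadjusted change: 2(1 − rho)s²
- baseline-adjusted: (1 − rho²)s²

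The ratio is (1 + rho)/2. Estimating the slope costs a factor of about 1 + 1/(N − 4) = 29/28 at N = 32. The number analysed by change that matches 32 adjusted completers is 32 divided by the corrected ratio. The article gives no rho, so a range is shown.

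| Assumed rho | Ratio (1 + rho)/2 | Corrected, N = 32 | Equivalent number by change | Power for 0.8 SD: change | Power for 0.8 SD: adjusted |
|---|---|---|---|---|---|
| 0.3 | 0.65 | 0.67 | 47.5 | 0.46 | 0.62 |
| 0.5 | 0.75 | 0.78 | 41.2 | 0.59 | 0.70 |
| 0.7 | 0.85 | 0.88 | 36.3 | 0.81 | 0.85 |
| 0.9 | 0.95 | 0.98 | 32.5 | above 0.99 | above 0.99 |

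Power is from the noncentral t, 16 per arm, two-sided 0.05, with 30 degrees of freedom for change and 29 for the adjusted comparison. At rho 0.5 the standard errors are √(1.0 × 2/16) = 0.354 SD for change and √(0.777 × 2/16) = 0.312 SD adjusted. For a 0.5 SD difference at rho 0.5, power is 0.28 against 0.34.

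**Simulation at rho 0.5 (20,000 trials of 16 per arm).** Variance was 0.125 for unadjusted change and 0.097 adjusted, a ratio of 0.77. Change analysed with baseline as covariate gave the same treatment estimate as the post value with baseline as covariate (largest difference 4 × 10⁻¹⁵).

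**Chance imbalance.** If the arms differ by D at baseline, the expected difference in change is off by −(1 − rho)D. With 16 per arm, D has a standard error of √(2/16) = 0.354 SD. At rho 0.5, an imbalance of that size moves the change comparison by 0.5 × 0.354 = 0.18 SD. Adjustment removes this.

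**The case against.** The strongest reply is that the article never says the comparison is unadjusted. Section 1.2 can be read as giving only the interval and direction of the hypotheses. The mixed ANOVA in section 2.9 is assigned to the main outcome. The model for exploratory outcomes may stand in an analysis plan that is not shown, and its absence from a journal article is no fault. This stands in part: a reader might infer that raw change is firmly prescribed, and the text does not go that far. What remains is that every pointer in the article leads to an unadjusted comparison. The measure is change, the only main model has no baseline term, and the adjusted model is tied to missing values.

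A second reply is that defining an outcome as change loses nothing. That is correct. A reader might infer that the definition itself costs precision, but change with baseline as covariate gives the identical treatment estimate. Rewording the endpoint without adding the covariate would achieve nothing.

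Third, the size is assumed, and near rho 0.9 the gain almost vanishes. Under randomisation the unadjusted comparison is also unbiased on average. The outcomes are exploratory, and section 2.9 sets its significance threshold for the primary outcome alone. All of this stands and limits the weight of the point.

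A reader might also want to extend the point to hypothesis b, the assessment by authorised personnel. The article does not give the scale on which that result is analysed, so nothing can be concluded about its model.

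**Conclusion.** The point holds as a free improvement of modest weight. Taken as written, c and d would be compared as unadjusted change, with a variance larger than that of the adjusted comparison by a factor of about 1.49, 1.29, 1.14 and 1.02 at assumed correlations of 0.3, 0.5, 0.7 and 0.9. These figures rest on equal SDs at both times, 16 completers per arm and a correlation that the article does not supply. The gain is worth having at low to moderate correlation and negligible at very high correlation. It does not follow that the secondary results would be biased on average or the trial undermined: the primary hypothesis, its analysis and the figures of 32 and 64 do not depend on this.

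**What to change.** In section 1.2, add to hypotheses c and d that the groups are compared on the post-intervention value (or, equivalently, on change) with the respective baseline value as covariate. In section 2.9, say that for the continuous questionnaire and EEG outcomes under c and d the baseline-adjusted model is the planned comparison, not only a sensitivity analysis when values are missing. With a single post-intervention value per person, this reduces to an analysis of covariance. For EEG, the recording before training serves as the baseline.

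The cost is a sentence in each place. No further data are needed, and the clinical question and sample size stay as they are.
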